### Follow-up

All the patients will undergo the same follow up: four visits within 1 year.

#### Control group:

Inclusion Visit: all the study data will be recorded and the inhalation technique will be tested.
Visit 1 will take place 3 months after the inclusion visit. Primary and secondary outcomes will be measured (excluding spirometry and quality of life).Visit 2 will take place 6 months after the inclusion visit. Primary and secondary outcomes will be measured (excluding spirometry and quality of life).Visit 3 will take place 12 months after the inclusion visit. All the study data will be recorded.

#### Intervention A group:

Inclusion Visit: all the study data will be recorded and the inhalation technique will be tested.
Visit 1 will take place 3 months after the inclusion visit. Primary and secondary outcomes will be measured (excluding spirometry and quality of life) and correct inhalation techniques using the designed leaflet will be encouraged.Visit 2 will take place 6 months after the inclusion visit. Primary and secondary outcomes (excluding spirometry and quality of life) and correct inhalation techniques using the designed leaflet will be encouraged.Visit 3 will take place 12 months after the inclusion visit. All the study data will be recorded and correct inhalation techniques using the designed leaflet will be encouraged.

#### Intervention B group:

Inclusion Visit: all the study data will be recorded and the inhalation technique will be tested.

Visit 1 will take place 3 months after the inclusion visit. Primary and secondary outcomes will be measured (excluding spirometry and quality of life) and encouraging correct inhalation techniques using the leaflet and the training with the monitor focusing on motivational aspects to enhance the individual skills of the patients will be individually applied.Visit 2 will take place 6 months after the inclusion visit. Primary and secondary outcomes will be measured (excluding spirometry and quality of life) and encouraging correct inhalation techniques using the leaflet and the training with the monitor focusing on motivational aspects to enhance the individual skills of the patients will be individually applied.Visit 3 will take place 12 months after the inclusion visit. All the study data will be recorded and encouraging correct inhalation techniques using the leaflet and the training with the monitor focusing on motivational aspects to enhance the individual skills of the patients will be individually applied.

A patient will be considered as being lost to follow-up if:
– The patient has not attended two follow-up visits– The patient has declined to continue in the study– The devices considered in the study have been withdrawn

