### Sample size

This has been calculated to detect a difference of 25% in correct inhalation technique between groups (Intervention A or B vs control), with a statistical power of 80% and a confidence level of 95%, assuming a percentage of expected losses of 40%. The final sample size is 296 patients with COPD who meet the inclusion criteria mentioned above.

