### Statistical Analysis

A descriptive statistical analysis will be performed for all the study variables. We will calculate the mean, median and standard deviations for quantitative variables, and the absolute and relative frequency for qualitative variables. The 95% confidence interval will be applied. A baseline comparison will be made between all groups to analyze the comparability using the chi-square test or ANOVA.

The analysis will be made following an intention-to-treat procedure [34].

The between-group comparison for the primary outcome will be explored using the chi-square test (Intervention A vs control; Intervention B vs control; Intervention A vs Intervention B).The Relative Risk Reduction (RRR), the Absolute Risk Reduction (ARR) and the Number Needed to Treat (NNT) will be calculated. Inferences for the secondary outcomes will be made using an analysis of variance (ANOVA) or chi-square test. Each group will be analyzed separately.

Finally, a logistic multivariate regression model will be performed for the primary outcome (performance of correct inhalation technique [yes/no]), considering the intervention as the predictive variable and the rest of the independent measures as the possible modifying factors.

We will use a 5% significance level (*p*=0.05). The SPSS 15.0 and Stata 11.1 statistical packages will be used to run the analysis.

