## Study limitations

One limitation of this study is the selection bias due to the missing data. In order to decrease this bias, we will apply several strategies:
An increase of 40% in the sample size (expected losses)Three phone calls on different days and times for unreachable patientsRescue appointments for the non-attendees to visits (three different appointment dates)In addition we take into account the possible contamination between the control and the intervention groups because of the relationship between subjects in their daily life (neighborhoods, relatives, social networks or associations). However, in another educational intervention study performed with obese patients in our area we did not find a significant level of this effect [35]. We also believe that the intervention characteristics (several steps and individual visits) that we have described will have little influence on contamination between groups.

In order to standardize interventions they will be performed by two professionals trained in communication, the knowledge of disease, and inhalation techniques of the different inhaler devices. Furthermore, we have designed a manual for the researchers where we explain the working plan, the different parts of the intervention, and the protocol in order that they know what they have to measure each time and the details to assess each variable included in the study. In this way, the procedure can be replicated elsewhere.

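### The loss-to-follow-up rule can write off randomised patients whose inhaler technique could still be scored, and a larger sample is wrongly listed as a way to reduce missing-data bias

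*Protocol article*

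**What the plan says.** The loss criteria stand at the end of the Follow-up section, under the Intervention B group, but are worded for any patient. There are three: "The patient has not attended two follow-up visits", a decision by the patient not to go on, and "The devices considered in the study have been withdrawn". The same section schedules follow-up visits at 3, 6 and 12 months in all arms, with the primary outcome (technique free of recorded mistakes) assessed at each.

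Statistical Analysis states: "The analysis will be made following an intention-to-treat procedure". It then plans pairwise chi-square tests and does not say how patients classed as lost enter them.

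Sample size allows for 40% losses: "The final sample size is 296 patients with COPD who meet the inclusion criteria mentioned above".

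Study limitations names selection bias from missing data and continues: "In order to decrease this bias, we will apply several strategies". Three measures follow: a sample enlarged by 40%, three telephone calls to patients who cannot be reached, and rescue appointments on three dates for those who miss a visit.

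**The concern.** Intention-to-treat compares patients as randomised and does not condition on what happens afterwards. Missing two visits and having a device withdrawn are both events after randomisation, and neither means that the outcome cannot be obtained. If meeting a criterion ends follow-up, outcomes that could have been collected are never collected, and no later analysis plan can recover them. The comparison then rests partly on who kept attending and who kept the same device.

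The second problem is separate. Attrition bias arises when the patients who remain differ from those who leave, in a way that differs between arms. A larger sample has the same mix of stayers and leavers. The biased difference keeps its size and is estimated more precisely. Listing the 40% allowance as a bias measure may give false reassurance about a trial that expects to lose two patients in five.

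**Working it through.** **1. The plan's own figure.** Inputs from the article: a 25-point difference, 80% power, 5% significance, 40% losses, three equal arms. Assumed: two-sided test, no continuity correction, and 25% correct in control. The sample-size section gives no control rate; 25% is taken from the Discussion, where up to 75% in the earlier study had incorrect technique.

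- n per arm = [1.96·√(2·0.375·0.625) + 0.842·√(0.25·0.75 + 0.50·0.50)]² / 0.25² = 57.7, so 58
- 3 × 58 = 174 evaluable; 174 / (1 − 0.40) = 290 (291 if rounded per arm), within 3% of 296
- 174 × 1.4 = 244, which does not match at these rates

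The inputs are not unique. For example, 35% vs 60% with a continuity correction and a 1.4 multiplier gives 70 × 3 × 1.4 = 294. Either kind of inflation treats lost patients as adding nothing to power. That suggests they are not expected to supply outcomes, but does not prove it.

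**2. Who meets the criteria while still measurable.**

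- Visit rule: nothing requires the 12-month visit to be one of the two missed. A patient absent at months 3 and 6 already qualifies, with month 12 still ahead.
- Device rule: it is independent of attendance. The patient may come to every visit.
- Patient declines to continue: the outcome may truly be unobtainable, so this criterion is not at issue.

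**3. Size of the visit rule.** Let m be the chance of missing any one visit, independent across visits (assumed; the article gives no such figure). The chance of missing months 3 and 6 but attending month 12 is m²(1 − m).

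| m | m²(1 − m) | × 296 |
|---|---|---|
| 0.20 | 3.2% | 9 |
| 0.25 | 4.7% | 14 |
| 0.30 | 6.3% | 19 |

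The planned losses are 0.40 × 296 ≈ 118, so this is about 8% to 16% of that number. The documents give nothing from which to size the device rule.

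**4. Does a larger sample reduce the bias?** Illustration with assumed rates: no true effect, 25% correct in both arms, 40% lost per arm. Losses are random in control; in the other arm the lost patients have a 10% correct rate.

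- Retained rate in that arm: (0.25 − 0.40 × 0.10) / 0.60 = 0.35
- False difference: 0.35 − 0.25 = 10 points, with no N in the formula
- Chance of a significant result: about 15% with 58 randomised per arm, 22% with 97, 54% with 296

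What the allowance does achieve is power. At 25% vs 50%, about 59 evaluable per arm (0.6 × 296 / 3) gives 0.81.

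**The case against.** The strongest reply is that the criteria only assign a label. A reader might infer that lost patients are removed and that the analysis is a completer analysis under an intention-to-treat name. The article says neither, and does not say that such patients stop being invited. Their handling may be set out in a full protocol or analysis plan not shown here. A chi-square test can be run on everyone randomised once a rule for missing values is fixed, and inflating N for losses is routine under any handling. This stands: a contradiction with intention-to-treat is not established, and the point has to be conditional.

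Other limits also stand:

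- The telephone calls and rescue appointments do address missingness. Oversampling is one of three measures, and the 9 to 19 patients would be fewer if rescue works.
- Device withdrawal can mean a switch, a stop or removal from the market. Where no inhaler remains in use, there may be nothing to score.
- One might suppose that withdrawal differs by arm because Intervention B discusses problems with technique. Nothing describes trial staff changing devices, so this is speculation.
- With 40% missing per arm and 50% vs 25% correct among those observed, the difference over all randomised patients could lie anywhere from 0.6 × 25 − 40 = −25 to 0.6 × 25 + 40 = +55 points. Those bounds belong to the whole 40% loss, not to this rule. If the 9 to 19 patients are among the 118, recovering them cuts missingness only to about 37% or 34%, with bounds of about −21 to +53 or −17 to +50.
- The article does not name 12 months as the primary time point.

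None of this removes the two defects in the text: a stated rule that can declare a patient lost before a visit that could still take place, and a power measure listed as a bias measure.

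**Conclusion.** The point holds in a limited form. As worded, two of the three criteria class randomised patients as lost for reasons other than an unobtainable outcome. If that label ends follow-up or analysis, which the 40% allowance suggests and the text does not state, the attrition is avoidable and fits poorly with the intention-to-treat statement. For the visit rule the size is modest: about 9 to 19 of 296 patients, assuming independent visits missed by 20% to 30% and no effect of rescue appointments. The device rule cannot be sized.

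The statement about oversampling is wrong without any such condition. A sample 40% larger protects power and leaves selection bias from missing data as it was. The 10-point illustration rests on assumed rates and shows the mechanism only; it does not predict the bias in this trial.

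**What to change.** - Separate missed visits and device withdrawal from loss to follow-up, recording each as an event in its own right.
- Seek the technique assessment at every remaining visit, including 12 months, from all randomised patients who have not withdrawn consent. Score the inhaler then in use, where there is one.
- Include every outcome obtained in the intention-to-treat comparison.
- Add a sensitivity analysis counting missing outcomes as incorrect. At 40% missing this turns an assumed 50% vs 25% into 0.6 × 50 = 30% vs 0.6 × 25 = 15%. Power at 98 per arm is then about 0.71 (121 per arm would be needed for 80%), so it should be read as a sensitivity check.
- In Study limitations, describe the 40% allowance as protecting power, and keep the telephone calls and rescue appointments as the measures against missing data.

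The cost is a few sentences of protocol wording, a few more appointments of the kind already planned, and slightly more analysis work. The sample size does not change.

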### Statistical Analysis

A descriptive statistical analysis will be performed for all the study variables. We will calculate the mean, median and standard deviations for quantitative variables, and the absolute and relative frequency for qualitative variables. The 95% confidence interval will be applied. A baseline comparison will be made between all groups to analyze the comparability using the chi-square test or ANOVA.

The analysis will be made following an intention-to-treat procedure [34].

The between-group comparison for the primary outcome will be explored using the chi-square test (Intervention A vs control; Intervention B vs control; Intervention A vs Intervention B).The Relative Risk Reduction (RRR), the Absolute Risk Reduction (ARR) and the Number Needed to Treat (NNT) will be calculated. Inferences for the secondary outcomes will be made using an analysis of variance (ANOVA) or chi-square test. Each group will be analyzed separately.

Finally, a logistic multivariate regression model will be performed for the primary outcome (performance of correct inhalation technique [yes/no]), considering the intervention as the predictive variable and the rest of the independent measures as the possible modifying factors.

We will use a 5% significance level (*p*=0.05). The SPSS 15.0 and Stata 11.1 statistical packages will be used to run the analysis.

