### Recruitment

Patients who meet the requirements described above will be contacted using their health center records. They will be invited to participate in the study after a brief explanation by telephone, and they will receive an appointment in the health center. At this first appointment (inclusion visit) patients will receive more detailed information about the study and if they agree to participate, they will sign the written consent.

At this point, they will be divided into three study groups: Intervention A, Intervention B and a control (Figure 1). The randomization will be made using the block randomization technique and applied separately at each study center. The blocks consist of six patients, two subjects per arm; or three patients, one subject per arm (Intervention A, Intervention B and control). The blocks will be marked with a number and they will be chosen at random to create the allocation sequence using a series of random numbers generated by a Microsoft Excel 2003 program. The person responsible for assigning patients to this group will make contact by phone. Because the patients will be from various health centers, the presence of the two interventions and control subjects in all the health centers will be guaranteed.

After randomization, all the study data will be recorded and the performance of correct inhalation techniques will be measured in all groups (inclusion visit). In the case of the control group, the inhalation techniques will be tested by asking patients about how they used their inhalers and the interviewer will write down the mistakes in the template. The interviewer will only correct the critical mistakes previously agreed by the research team and all interviewers who participate in the study. In the follow-up visits the subjects will be invited to perform the inhalation technique and the mistakes will be written down. The appointments last approximately 20–30 minutes, depending on the study arm.

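### The sentence that each group is analysed separately leaves the secondary outcomes without a stated between-arm comparison

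*Protocol article*

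**What the plan says.** The Statistical Analysis section treats the two classes of outcome differently.

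- **Primary outcome.** "The between-group comparison for the primary outcome will be explored using the chi-square test", followed by three named contrasts: A versus control, B versus control and A versus B. Later, "a logistic multivariate regression model will be performed for the primary outcome", with the intervention as predictor.
- **Secondary outcomes.** "Inferences for the secondary outcomes will be made using an analysis of variance (ANOVA) or chi-square test". The next sentence is "Each group will be analyzed separately". No contrast between arms is named.
- **Baseline.** The only stated use of baseline values is a check of comparability: "A baseline comparison will be made between all groups to analyze the comparability using the chi-square test or ANOVA".

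The Follow-up section shows what data exist. At entry, in the same words for every arm: "Inclusion Visit: all the study data will be recorded and the inhalation technique will be tested". Secondary outcomes are measured again at 3, 6 and 12 months, except spirometry and quality of life, which are repeated only at 12 months.

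**The concern.** A within-arm analysis asks whether patients in one arm changed. The trial is meant to answer whether they changed more than patients in another arm. A significant change in B beside a non-significant change in control is not evidence that B and control differ. Two significant changes are not evidence that either intervention worked.

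This design invites the confusion. Control patients are assessed at the same four visits, and under Recruitment the interviewer corrects their agreed critical mistakes, so they may improve too. The Background describes COPD as a disease that usually progresses, so a real benefit might appear only as slower decline and be missed within an arm. The Discussion faults the authors' earlier study for lacking a control group and justifies randomisation as the way to rule out other explanations of change over time. Separate-arm inference would give that protection up for peak flow, spirometry, dyspnoea and quality of life.

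**Working it through.** **1. What the two readings give**

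| Reading of the sentence | Consequence |
|---|---|
| Each arm is tested on its own, for instance across visits | No estimate of A or B against control |
| ANOVA or chi-square between the three arms | Estimates the randomised comparison, but the sentence then contradicts the test named |

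Both readings call for a change of wording. Only the first affects validity.

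**2. Inputs**

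- From the article: 296 patients, equal allocation to three arms, 40% expected losses, 5% significance level. Sidedness is not stated; two-sided is assumed.
- Patients per arm with data: 296/3 = 98.7, and 98.7 × 0.60 = 59.2, so about 59.
- Not in the article: any standard deviation, effect, correlation or power for a secondary outcome. These are assumed below and shown as ranges.

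The only figure the plan states is the total for the primary outcome. With an assumed 25% correct in controls against 50%, two-sided 5% and 80% power, the usual two-proportion formula gives 58 per arm. Then 58/0.60 = 96.7, rounded up to 97, and 3 × 97 = 291, within 2% of 296. The point made here does not depend on that total.

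**3. Separate tests when the arms do not differ**

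Let all arms change by the same amount, and let p be the chance that a within-arm test is significant. The arms contain different patients, so the tests are independent:

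- P(B significant, control not) = p(1-p)
- P(the three arms do not all agree) = 1 - p³ - (1-p)³ = 3p(1-p)

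| p (assumed) | B significant, control not | Three arms disagree |
|---|---|---|
| 0.50 | 25% | 75% |
| 0.80 | 16% | 48% |
| 0.90 | 9% | 27% |

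The first row is the maximum of both formulas. At p = 0.05 or p = 0.95, p(1-p) = 4.75%, so the excess over 5% arises when p lies roughly between those values.

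**4. Simulation check**

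20,000 trials per scenario, two arms of 59, the same mean change in both, changes in units of the outcome's standard deviation, r the assumed correlation between baseline and follow-up. The between-arm test is a t-test on the changes.

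| Common change | r | Intervention arm significant | Intervention significant, control not | Between-arm test significant |
|---|---|---|---|---|
| 0.2 SD | 0.5 | 33% | 22% | 5.1% |
| 0.3 SD | 0.5 | 62% | 24% | 5.1% |
| 0.2 SD | 0.7 | 49% | 25% | 5.1% |
| 0.3 SD | 0.7 | 83% | 14% | 4.7% |
| 0.5 SD | 0.5 | 97% | 3.5% | 5.0% |
| 0.5 SD | 0.7 | over 99% | 0.2% | 4.9% |

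At a common change of 0.5 SD the discordant pattern becomes rare, but nearly every trial then shows a significant change in the intervention arm with no intervention effect at all. The direct comparison stays near 5% throughout.

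**5. What baseline adjustment adds**

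An unadjusted between-arm comparison is already valid. ANCOVA multiplies the variance of the arm difference by about 1 - r², relative to follow-up values alone:

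- r = 0.3: 1 - 0.09 = 0.91
- r = 0.5: 1 - 0.25 = 0.75
- r = 0.7: 1 - 0.49 = 0.51

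At 59 per arm and an assumed difference of 0.5 SD, power is 77.5% on follow-up values alone, and 81%, 88% and 97% with adjustment at these three correlations.

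**The case against.** The strongest reply is that the section never mentions paired tests, within-arm tests or change over time. It names ANOVA and chi-square, the same pair it uses for the baseline comparison between all groups. With three arms these are ordinary between-group tests. An analyst planning before-and-after tests would more naturally name a paired t-test, Wilcoxon or McNemar test. The sentence may mean only that A and B are not pooled, which is a fair thing to clarify when the hypothesis is worded as A or B. This stands in part: the within-arm reading is plausible but not certain. It does not save the sentence, because the article does not say that pooling is what it excludes, and an analyst who followed it literally would be compliant.

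A second reply is that a condensed article may leave the choice of covariates to a fuller document. That also stands. Silence on baseline adjustment is not a defect. The finding rests on a sentence the article does contain.

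A reader might also infer that an analysis without baseline adjustment fails to estimate the randomised effect. It does not fail: under randomisation the unadjusted comparison estimates that effect and loses only precision. Nor may 75% and 25% be taken as the expected size of the problem. They are the largest values possible, at an assumed power of 50%, and apply only under the literal reading.

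**Conclusion.** The point holds as a badly worded rule of moderate importance, confined to the secondary outcomes. Either the sentence puts within-arm inference in place of the randomised comparison, or it contradicts the test named just before it. The documents do not support the stronger claim that the plan has definitely abandoned between-arm comparison.

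If the arms are tested separately and change equally, the misleading pattern in one intervention arm against control occurs in 9% to 25% of trials for within-arm power between 90% and 50%. A direct test errs in about 5%. These figures rest on assumed power, because the article gives no secondary-outcome inputs. The primary outcome has explicit between-arm contrasts, and neither its analysis nor the total of 296 is affected.

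**What to change.** Delete the sentence. In its place, state that each secondary outcome will be compared between the randomised arms (A versus control, B versus control, A versus B), with the estimated difference and its 95% confidence interval. If the intention was only that A and B are not pooled, say that.

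For quantitative outcomes, preferably adjust for the inclusion-visit value and for centre, since randomisation is applied separately at each centre. Present this as a gain in precision. For binary outcomes, a logistic model with the same terms is the counterpart. Where 3- and 6-month values are collected, the model can use them; it need not be limited to 12 months. Within-arm changes may still be reported descriptively.

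The cost is a change of wording and a little more analysis. No new data, visits or patients are needed.

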### Outcomes

*Primary outcome*: Performance of correct inhalation technique. This will be measured using a template designed following SEPAR (Sociedad Española de Neumología y CirugíaTorácica) guidelines [16] where the interviewer will write down any mistakes. It will be considered a good technique when there are no mistakes registered in the template.

*Secondary outcome:* Participants will be evaluated using inhaler peak flow, functional status (spirometry), mental-cognitive status (mini-mental state examination), dyspnea with the Baseline Dyspnea Index (BDI) [28] and Modified Medical Research Council (MMRC) scale [29]; questionnaires on quality of life (St George’s Respiratory Questionnaire [30], and EuroQoL-5D [31]) and the clinical progress of illness (SeguiEPOC questionnaire) will be recorded.

*Independent* v*ariables:* Independent variables will be: sex, age, educational level, smoking history, comorbidity, COPD severity grade (according to GOLD guidelines [24]), prescribed medication, type and number of devices, family support (Family Apgar Test [32]), and social support (DUKE-UNC Test [33]).

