## Discussion

Previous to this study, we designed and developed a multifactorial intervention to improve adherence in COPD, the ICEPOC study [36]. This study allowed us to analyze the motives and barriers that these patients experience in complying with the recommended medication regimens. The multifactorial intervention included training about inhalation techniques and we could see that up to 75% of patients did not perform them correctly. After the intervention we found that 17% still did not perform a correct inhalation technique [11] (52% of the patients in the intervention group enhanced their inhalation technique). But this study did not have a control group. So we designed a randomized controlled trial to define the role of the educational interventions over inhalation techniques. A randomized controlled trial (RCT) is regarded as the gold standard for assessing the effectiveness of treatment. It has the power to eliminate a variety of alternative explanations for changes in health-related measures over time, permitting the researcher to reasonably conclude that the intervention itself caused the changes.

The NICE and the GOLD guidelines recommend that prior to prescription of a new inhaler for a patient with COPD, the patient should receive training and education in the use of the device. Both guidelines also advise that inhaler technique should be regularly assessed at each clinic visit [24,25]. Written instructions alone are insufficient in teaching correct inhalation techniques. Verbal instruction and technique assessment and reassessment are essential for patients to achieve a correct technique [26].

Our hypothesis is that the application of educational interventions (Intervention A or Intervention B) in patients with COPD with inhaler therapy is going to help up to 25% of patients, who have been misusing their inhalers, improve their inhalation technique. These interventions are feasible to implement in the clinical practice context. With this strategy we are trying to promote patients’ autonomy and responsibility about their disease, achieving in this way a greater improvement on their health outcomes and increasing clinical effectiveness in our daily practice.

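### Neither the primary chi-square nor the supporting logistic model uses baseline inhalation technique or centre, so some precision is forgone; the comparison remains valid

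*Protocol article*

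**What the plan says.** The Statistical Analysis section of the protocol article compares the arms two at a time with a chi-square test on correct technique (A vs control, B vs control, A vs B) and derives ARR, RRR and NNT from it. A logistic model follows, "considering the intervention as the predictive variable and the rest of the independent measures as the possible modifying factors". The Outcomes section lists those measures, beginning "sex, age, educational level, smoking history, comorbidity, COPD severity grade" and continuing with medication, type and number of devices, and family and social support. Baseline technique and centre are not in the list.

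Both are nevertheless available. At the control group's inclusion visit "all the study data will be recorded and the inhalation technique will be tested", and the Follow-up section says the same for Interventions A and B. On allocation, the Recruitment section says: "The randomization will be made using the block randomization technique and applied separately at each study center". The only stated use of baseline data as such is a comparability check between groups.

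**The concern.** No inclusion criterion requires poor technique, so some patients will enter with a correct technique and have nothing to gain on a yes/no outcome. In the earlier study described in the Discussion, "we could see that up to 75% of patients did not perform them correctly"; the Background cites over 80% incorrect, and one study with 5 of 60 patients (8.3%) fully correct. If technique at entry predicts technique later, leaving it out of the model widens the confidence interval, and any chance imbalance in it feeds into the estimate without correction. Leaving out the randomisation stratum makes the standard error slightly too large when centres differ. The article fixes both the test and the covariate list, so this is a stated choice and not detail deferred to an unseen plan.

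**Working it through.** **Inputs.** From the article: total 296, 40% losses, 80% power, a 25-point difference ("This has been calculated to detect a difference of 25% in correct inhalation technique between groups"), a 5% level, 1:1:1 allocation, seven centres. Assumed: two-sided testing; 25% correct in controls (the complement of 75%); 25% correct at entry; the strength of the baseline-to-follow-up association; the spread between centres.

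**1. The plan's own figure.** Two proportions, 25% vs 50%, no continuity correction:

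n = [1.96·√(2·0.375·0.625) + 0.8416·√(0.25·0.75 + 0.50·0.50)]² / 0.25² = (1.342 + 0.557)² / 0.0625 ≈ 57.7, so 58 per arm.

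3 × 58 = 174, and 174 / 0.6 = 290 (291 if rounded per arm), within 3% of 296. Conversely, 296 × 0.6 / 3 ≈ 59 evaluable per arm. The match depends on the assumed control rate: 20% gives 270 and 37.5% gives 310.

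**2. Unadjusted power.** At 59 per arm, 25% vs 50%: 80.9%. The standard error is √[(0.1875 + 0.25)/59] = 0.086.

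**3. Baseline technique, general approximation.** With correlation phi between baseline and follow-up technique, effective n = 59/(1 − phi²):

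| phi | effective n per arm | power |
|---|---|---|
| 0.2 | 61.5 | 82.5% |
| 0.3 | 64.8 | 84.5% |
| 0.4 | 70.2 | 87.3% |
| 0.5 | 78.7 | 90.7% |

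This takes phi to be the same in both arms.

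**4. Baseline technique, with and without benefit in patients already correct.** Three control-arm patterns each give 25% correct overall, for example 0.25 × 70% + 0.75 × 10% = 25%. If patients correct at entry gain nothing, those incorrect at entry must reach (0.50 − 0.25 × 0.70)/0.75 = 43.3% for the intervention arm to reach 50%. Simulated power of a risk-difference model with robust standard errors, no benefit in those already correct:

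| Later correct in controls (correct / incorrect at entry) | Intervention arm, incorrect at entry | Unadjusted | Adjusted |
|---|---|---|---|
| Strong, 70% / 10% | 43.3% | 0.81 | 0.88 |
| Moderate, 55% / 15% | 48.3% | 0.82 | 0.84 |
| Weak, 40% / 20% | 53.3% | 0.81 | 0.81 |

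The gains are about 8, 3 and under 1 points; the standard error in the strong case falls from 0.086 to 0.079. If everyone gains 25 points whatever their entry status, adjusted power is 0.92 to 0.93, 0.86 and 0.82, and the strong-case standard error is 0.072 to 0.073. The gain shrinks without benefit in the already-correct because the baseline association weakens in the treated arm (55% vs 48.3% in the moderate row) or reverses (40% vs 53.3% in the weak row).

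**5. Centre.** Simulated with phi 0: no real change if centres do not differ; 81.0% to 82.7% at a between-centre SD of 0.10 on the probability scale; 80.4% to 83.7% at 0.15. Under the null with SD 0.15 and phi 0.3, the unadjusted test rejects 4.1% instead of 5% (mean standard error 0.080 against a true 0.077), so it is mildly conservative.

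**The case against.** The strongest reply is that nothing is wrong. Under randomisation the unadjusted chi-square is valid for the marginal risk difference, its type I error already allows for chance imbalance, and it delivers the planned power. That stands, and it limits the point to efficiency. A reader might infer that the trial is biased or underpowered without adjustment; the article's own figures do not support that.

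A second reply concerns size. The article gives neither the predictive strength of baseline technique nor the variation between centres. A reader might take power of about 92% as the expected result of adjustment, but that needs a strong association and a full 25-point gain in patients who are already correct, which sits badly with the idea that they cannot improve. The Discussion's post-training figure of 17% incorrect also caps the association. With 25% correct at entry and 83% afterwards, the largest possible phi is √[(0.25 × 0.17)/(0.83 × 0.75)] = 0.26. This reply stands.

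A third reply is that baseline technique may not be a clean covariate. The Recruitment section records it after randomisation and describes controls as being asked how they used their inhalers. Under Intervention, A patients show their technique, and B patients show it with placebo inhalers. Adjusting for a post-randomisation measure taken differently by arm could bias a comparison that is now unbiased. This stands as a condition on the remedy.

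Finally, a reader might conclude that the logistic model with all 11 listed variables cannot be estimated. About 20 main-effect terms and some 65 correct techniques, 59 × (0.25 + 0.35 + 0.50), would leave about 3 events per term. But the 20 terms rest on assumed category counts and the 35% in arm A is not in the article. Calling the variables possible modifying factors does not commit the analysts to entering all of them at once with interactions.

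**Conclusion.** The point holds as forgone precision. Both outcome analyses leave out a covariate that is measured in every arm and the factor within which patients are randomised. Under the assumed rates and 59 evaluable per arm, adjusting for baseline technique is worth roughly 0 to 8 points of power if patients correct at entry do not benefit. The upper limit is about 12 if they benefit equally and baseline is strongly predictive. Centre is worth about 0 to 3 points, and ignoring it errs on the conservative side. These figures come from a risk-difference model and are only an approximate guide to a logistic model. The case for change is that the gain needs no additional patients or data items, provided baseline technique is measured comparably across arms.

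**What to change.** Make the primary analysis a regression of correct technique, at the visit designated primary, on arm, baseline technique (correct/incorrect) and centre. Report a standardised (marginal) risk difference with 95% CI for each comparison, and keep the chi-square as a supporting analysis. The model has 2 + 1 + 6 = 9 terms, or about 7 events per term at 65 events. Use regression rather than cross-stratification: in simulation (phi 0.3, centre SD 0.10) a Mantel-Haenszel test over 14 baseline-by-centre strata had 83.3% power against 85.1% with baseline strata alone.

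State that baseline technique is assessed with the same demonstration and template in all arms, before any leaflet, training or correction and preferably before allocation is revealed. If that cannot be assured, adjust for centre only in the primary analysis. Describe the other independent variables as exploratory modifiers.

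The cost is wording in the analysis section, plus an aligned inclusion-visit procedure in the researchers' manual if assessment currently differs by arm. No new data item is needed.
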